#### Client implementation outcomes

Feasibility is assessed by examining intervention recruitment, attendance, and retention rates as well as survey attrition. We assess acceptability of the client intervention using 12 internally developed items that are administered in an anonymous survey after each treatment session that clients attend. Items ask about comfort level with the material and how useful and relevant the group content is. Responses are rated on Likert scales ranging from 1 to 5, with total scores ranging from 12 to 60 and higher scores indicating more acceptability. There are also open-ended questions asking about suggestions for improvement.

### Data analysis plan

#### Preliminary analyses

All data will be entered directly into the Redcap survey platform (directly by staff completing the online survey, via research staff manual entry during phone interviews with clients). Data will be exported, cleaned, and managed using Statistical Package for the Social Sciences (SPSS). Data from all counties will be pooled for staff and client assessments. We will run descriptive statistics (i.e., ranges, means, frequencies) and transform variables to achieve normality as needed.

#### Implementation

Feasibility will be analyzed by calculating client and staff consent and refusal rates, attendance, participation (i.e., in-group discussion), pre- and post-survey completion, and follow-up attrition, as well as review of intervention delivery technical issues. To understand the acceptability of staff and client intervention content, we will aggregate anonymous feedback data. Qualitative data from staff focus groups will be aggregated, coded, and interpreted to better understand implementation barriers and facilitators using a top-down content analysis approach (Hsieh and Shannon, 2005) in Nvivo software.

#### Effectiveness

Pre- to post- change in staff and client assessments will be analyzed using repeated measures factorial ANOVAs that compare pre, post-, 1-month, and 3-month follow-up data for clients and staff. Tukey’s posthoc comparisons will be used to pinpoint significant mean differences between timepoints. We will examine main and interaction effects to test whether mean differences in staff assessments depend on type of profession (assuming adequate sample sizes). Omega squared effect size estimates will be computed. We will control for relevant staff- and client-level variables. Additional analyses may include testing whether client and staff change scores (3-month survey score subtracted from pre-test) predict TN-ROCS program-level outcomes such as retention and disciplinary infractions. Significant effects will be designated by *p* < 0.10 and meaningful effect size estimates.

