### Participants and procedures

#### CSTARR-staff

The CSTARR-staff intervention is scheduled according to each county’s court calendar to facilitate TN-ROCS staff availability. To recruit our target sample of 72 staff across 6 counties, the judge in each county will distribute an advertisement for the CSTARR-staff training that includes a link to register. Staff will be strongly encouraged to participate but not required to. When staff register, they will automatically be sent the training details (via Zoom) and then emailed an invitation to complete the online baseline survey which includes the informed consent. Staff are permitted to register and attend the training without completing the baseline survey. Any staff affiliated with the TN-ROCS program who have interacted (either virtually or in- person) with a TN-ROCS client in the past 90 days are eligible to participate. Staff are asked to complete an anonymous feedback survey during the last 10 min of the training and are sent a link to complete the post-test survey at that time. Staff are automatically emailed with the one-month and three-month follow-up survey links. For completing the pre- and post-test surveys, staff receive a $5 e-gift card. For the follow-up surveys, they are emailed a $10 gift card. We anticipate retaining 75% of staff by the 3-month follow up. The training is audio-recorded. We will continue to approach staff for follow-up regardless of missing data at a prior timepoint. Email and phone call reminders will be used to increase completion of online surveys.

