#### CSTARR-client

To recruit our target sample of 72 TN-ROCS clients across 6 counties (i.e., approximately 12 per county), each county’s CJL will distribute a study advertisement when doing treatment intakes with new clients. CJLs (and judges) will strongly encourage clients to consider participating but it will not be required as part of their involvement in TN-ROCS. Interested clients sign a recruitment waiver so their contact details can be released to the research team. The Project Coordinator then contacts clients via phone to have an in-depth discussion of procedures, risks, benefits, and human subjects protections as part of the informed consent process. Consented clients then proceed to complete their baseline interview over the phone. Any TN-ROCS clients (i.e., arrested, have evidence of substance use problems, are accepted into the TN-ROCS program), will be eligible except those deemed by the CJL to have debilitating mental illness or violence risk. There are no exclusion criteria around stigma (e.g., those reporting low self-stigma) in order to gauge CSTARR utility for all clients. At the end of each intervention session, clients are asked to complete an anonymous online feedback form, and their post-test survey (completed over the phone with a research assistant) is scheduled to take place immediately after the last intervention session. Participants receive a $5 giftcard for the baseline and post-test interviews, and a $10 gift card for the 1- and 3-month follow up assessments. To offset the time and logistical burden of completing the intervention, participants will receive up to $30 in gift cards if they attend the entire intervention. All group sessions are audio-recorded. We anticipate retaining 75% of clients across the 3 sessions and 50% by the 3-month follow-up. We continue to approach clients for follow-up regardless of missing data at a prior timepoint. Phone calls, texts, and/or email reminders are used to increase completion of surveys.

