#### Primary client outcomes

We will examine change from the baseline to the 3-month follow-up timepoint in the following measures:Self-stigma. We will use the Substance Abuse Self-Stigma Scale (SASS) ([name] et al., 2013) to assess self-stigma associated with substance use and criminal involvement. The SASS is a 41-item measure that assesses self-devaluation, fear of experiencing stigma, avoidance of stigma, and values disengagement among people with substance use problems. Responses are rated on a scale from 1 (never or almost never) to 5 (very often), with total scores ranging from 41 to 205 and higher scores indicating more self-stigma. We adapted this measure to ask about both criminal involvement and substance use stigma within the items in this measure (e.g., “People think I’m worthless if they know about my substance use or criminal history”). The SASS scale has been shown to be reliable and valid for assessing self-stigma among people with substance use problems (Brown et al., 2015; [name] et al., 2013).Shame. The Internalized Shame Scale (ISS) (Cook (n.d.)) is a 24-item measure that includes shame-related thoughts and experiences, which are considered central to self-stigma. Responses are rated from 0 to 4, where 0 is never and 4 is almost always, with the total score ranging from 40–120 and higher scores indicating more internalized shame. The ISS has been used to track changes in shame across clinical interventions, including ACT for substance use self-stigma ([name] et al., 2013) and is shown to be reliable and valid in a variety of clinical and non-clinical samples (Goffnett et al., 2020; Rybak & Brown, 1996).Self-efficacy. We use a 1-item internally developed measure to assess the degree to which clients feel they can cope with unfair judgments from the community regarding their substance use or criminal history. The item is rated on a scale from 1 to 10, with 1 being lowest expectation of success and 10 being the highest expectation of success.Coping skills. We use 28 items from the Dialectical Behavior Therapy Ways of Coping Checklist (DBT-WCCL) (Neacsiu et al., 2010) to assess client use of specific skills being taught in the CSTARR-client intervention. The DBT-WCCL is originally a 59-item measure that captures client use of adaptive and maladaptive coping skills and is widely used among people attending DBT skills interventions, which is another third-wave behavioral therapy similar to ACT. This measure has been used to assess improvement across treatment among people with various degrees/severity of mental illness (Brown et al., 2019; Kells et al., 2020; Stein et al., 2016). We utilize items that capture skills being taught in CSTARR-client (e.g., engaging in valued actions, acceptance of thoughts and feelings, emotion regulation techniques such as relaxation) as well as maladaptive coping skills we believe CSTARR-client may reduce, such as externalization of blame, avoidance, and social withdrawal/isolation.

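### The four-wave repeated measures ANOVA can use at most 36 of 72 clients and 54 of 72 staff under the plan's own retention forecast, and it drops people who have both scores needed for the primary change

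*Protocol article*

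**What the plan says.** Under Data analysis plan, Effectiveness, the protocol article fixes the method: change in the staff and client measures "will be analyzed using repeated measures factorial ANOVAs that compare pre, post-, 1-month, and 3-month follow-up data for clients and staff". The same paragraph then adds a second step by Tukey's method, in which "posthoc comparisons will be used to pinpoint significant mean differences between timepoints".

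The primary client outcomes are defined by one contrast: "We will examine change from the baseline to the 3-month follow-up timepoint in the following measures". The primary staff outcomes use the same baseline-to-3-month contrast.

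The retention forecast stands under Participants and procedures. For clients: "To recruit our target sample of 72 TN-ROCS clients across 6 counties (i.e., approximately 12 per county"), and "We anticipate retaining 75% of clients across the 3 sessions and 50% by the 3-month follow-up". For staff: "To recruit our target sample of 72 staff across 6 counties", and "We anticipate retaining 75% of staff by the 3-month follow up".

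The follow-up procedure allows for gaps: "We continue to approach clients for follow-up regardless of missing data at a prior timepoint". The CSTARR-staff section says the same of staff, and also lets staff attend the training without a baseline survey.

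The article names no imputation, mixed model or other means of keeping incomplete records. Under Implementation, follow-up attrition appears as a feasibility measure.

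**The concern.** The named analysis and the planned data collection do not fit together. A repeated measures ANOVA in its classical form works on a complete row per person, so a participant who misses one of the four waves is lost to the whole analysis. The plan forecasts substantial loss by 3 months and pays for follow-up surveys from people who missed an earlier one. A client who skips the 1-month interview but completes baseline and 3 months has exactly the two scores that define the primary outcome, and the stated model still sets that client aside.

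Two things are at stake. The first is precision, since the estimate rests on fewer people than supplied usable data. The second is possible selection. If those who complete every wave differ in outcome from those who do not, the estimated change describes the completers. Effectiveness is a secondary, preliminary goal, but the abstract says that the results will inform a larger randomized trial.

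**Working it through.** **Inputs from the protocol.** Target 6 counties × 12 = 72 clients, which reproduces the stated target; target 72 staff. Retention at 3 months: 50% of clients, 75% of staff. Client retention across the sessions: 75%.

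**Inputs assumed here.** Within-person correlation (0.6, range 0.5 to 0.7, equal between all waves), unit variance at each wave, and the completion rates marked as assumed below. The 75% for client sessions describes attendance; using it as the post-test completion rate is also an assumption.

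**Step 1: ceiling on complete records.** Nobody can have all four scores without the 3-month score.
- Clients: 72 × 0.50 = 36.
- Staff: 72 × 0.75 = 54.
- If the 50% is read as a share of the 75% retained in sessions: 72 × 0.75 × 0.50 = 27 clients.

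**Step 2: effect of intermittent gaps.** If waves are missed independently:
- Clients, assumed 75%, 60% and 50% at post-test, 1 month and 3 months: 72 × 0.75 × 0.60 × 0.50 = 16.2. About 36 would still have baseline and 3-month scores, so about 36 − 16.2 = 19.8 people with the primary contrast would be dropped.
- Clients, with 1-month completion varied from 50% to 75%: 13.5 to 20.3.
- Staff, assumed 90% at post-test and 75% to 100% at 1 month: 72 × 0.90 × 0.75 × 0.75 = 36.5, up to 72 × 0.90 × 1.00 × 0.75 = 48.6.

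**Step 3: precision of the client baseline-to-3-month change.** Complete-case variance is 2(1 − ρ)/n. For the all-data model, the variance is that of the same contrast from the inverse of the information summed over the expected missing-data patterns, with the covariance taken as known.

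| Pattern (ρ = 0.6) | Complete cases | Complete-case SE | All-data SE | Variance ratio |
|---|---|---|---|---|
| Monotone, 72/54/43/36 at the four waves | 36 | √(0.8/36) = 0.149 | 0.138 | 0.85 |
| Independent, 75%/60%/50% | 16.2 | √(0.8/16.2) = 0.222 | 0.136 | 0.38 |

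For ρ from 0.5 to 0.7 the ratio runs from 0.84 to 0.87 (monotone) and from 0.37 to 0.38 (independent).

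**Step 4: possible bias.** Simulation of 72 clients with assumed correlation 0.5, monotone dropout calibrated to 75% at post-test and 50% at 3 months, and a true change of −0.30 SD. Dropout depended on the last observed score, with an assumed log-odds slope per SD.

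| Slope | Complete-case estimate | All-data likelihood estimate |
|---|---|---|
| 0 | −0.30 | −0.30 |
| 0.7 | −0.23 | −0.30 |
| 1.4 | −0.19 | −0.30 |

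The bias is nil when dropout is completely random and about 0.07 to 0.11 SD in the other two scenarios. The simulated dropout depends only on observed scores, which is the condition under which the likelihood analysis is valid, so its good showing there is by construction.

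**The case against.** **The article does not say that incomplete records are deleted.** It names a family of tests, and a separate analysis plan could add imputation. That is fair, and silence on missing data would not by itself be a point against a condensed article. The point here is narrower: the method that is named needs complete rows, and the same article forecasts that half of the clients will not have them.

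**The precision loss depends on the pattern.** This stands. Under monotone dropout, the standard error falls only from 0.149 to 0.138, about 8%. The much larger gain needs independent missingness, which is an assumption. Continued approach after a missed wave makes some gaps likely, but nothing says how many.

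**A reader might infer that the result will be biased, or that it will flatter the intervention because completers do better.** The document supports neither. Bias requires dropout related to outcome. That is plausible in a court-supervised program where non-compliance can lead to jail, but it is not shown. In the simulated scenarios the complete-case estimate understated the improvement.

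**A reader might also infer that Tukey's comparisons will inflate the standard errors by ignoring the pairing of scores.** That needs time to be treated as a between-person factor. The plan says repeated measures and nowhere suggests it, so no such inflation is claimed.

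**Effectiveness is secondary.** The main goal is feasibility and acceptability, and the article already limits its effectiveness claims for lack of a control group. Intermittent responders still count toward feasibility and the secondary client outcomes, and the optional change-score analyses need only two waves. This lowers the stakes. It does not make the four-wave ANOVA a good match for the measures that the plan labels primary.

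**Conclusion.** The point holds as a mismatch between the named analysis and the plan's own retention forecast. The ceilings of 36 of 72 clients and 54 of 72 staff follow from the stated figures, taking retention as a share of all enrolled and assuming no imputation. Intermittent gaps lower both numbers and remove people who hold the primary contrast.

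The cost in precision lies between modest and large: the all-data model has about 85% of the complete-case variance under monotone dropout and about 38% under independent missingness at the assumed rates. Bias is a conditional risk of unknown size and direction. Because the remedy costs almost nothing, the change is worth making even at the modest end.

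**What to change.** Replace the repeated measures ANOVA under Effectiveness with a likelihood-based linear mixed model for repeated measures:
- time as a four-level categorical factor, with within-person correlation modelled, and profession and its interaction with time retained for staff where numbers allow;
- every participant with any score included;
- the baseline-to-3-month contrast reported with its confidence interval as the main effectiveness result;
- other time contrasts taken from the same model with a Holm or Bonferroni adjustment, in place of Tukey's comparisons;
- the missing-at-random assumption stated.

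For clients, add one sensitivity analysis for data not missing at random, for example by TN-ROCS enrolment status. Clients report this at follow-up, and liaisons are asked for it when a client cannot be reached (Secondary client outcomes). It records program enrolment rather than survey dropout, so it is an imperfect marker, and the article describes no equivalent for staff.

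The cost is a change of analysis wording and the use of a mixed-model routine. No new data are needed, and the article describes data collection as ongoing, so the change can be made before analysis.

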## Interventions to reduce the stigma of substance use and criminal involvement

### Social/public stigma

Social stigma (also referred to as public stigma) surrounding substance use and criminal involvement is driven by a range of factors, including lack of knowledge, familiarity, and empathy, as well as harmful institutional norms (Nieweglowski et al., 2018; Nyblade et al., 2019; Rade et al., 2016). Although there are several existing interventions designed to reduce substance use stigma among healthcare and other professionals (Crapanzano et al., 2014; Livingston et al., 2012), there are considerable gaps in these trainings. First, the majority rely primarily on education-based strategies which provide information about the science of addiction, treatment, and recovery. Although educational interventions have been shown to increase knowledge, numerous studies have shown that education alone does not produce lasting changes in stigma (Corrigan et al., 2015a), and that strategies which facilitate positive interactions between non-stigmatized and stigmatized people who have lived experience (e.g., history of substance use) have longer-lasting effects (Corrigan, 2017). Second, most if not all existing stigma interventions emphasize changing stigmatizing attitudes and beliefs as the primary goal, with outcome measures reflecting this focus (Mittal et al., 2012). Decades of psychological research suggests that attitude change is not only challenging, but potentially not as meaningful as behavior change (Hayes, 2004). Despite this, stigma interventions focus almost exclusively on attitude change. Finally, to our knowledge, no existing interventions (at any level) have attempted to address the intersection of substance use with criminal involvement stigma, the latter of which has been shown to be more predictive of criminal legal staff’s negative attitudes toward addiction treatment ([name] et al., 2022). Moreover, criminal involvement stigma (e.g., believing that people who get arrested are different/bad, unable to be rehabilitated, dangerous, untrustworthy) has been well-documented among the general public, employers, criminal legal professionals, and healthcare workers, and is harmful to the health and adjustment of people involved in the legal system (Griffith et al., 2019; Martin et al., 2020; Pager et al., 2009; Pogorzelski et al., 2005). Stigma surrounding criminal involvement becomes particularly problematic when it interferes with providing evidence-based care for substance use. Specifically, beliefs that people with substance use disorders who get arrested deserve punishment rather than treatment, and expectations that people in the criminal legal system will never recover can prevent legal settings from facilitating access to high-quality addiction treatment. Taken together, these gaps suggest the need for a multi-level intervention targeting social/public stigma among criminal legal staff that addresses substance use *and* criminal involvement stigma, psychoeducation *and* contact with stigmatized people who have lived experience of addiction/incarceration, and a focus on behavioral *in addition to* attitudinal change.

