### Interventions

#### Content and structure

At the staff level (CSTARR-staff), CSTARR involves a 4-h synchronous virtual training delivered via Zoom videoconferencing software, by the PI ([name]) along with a certified peer recovery specialist. The training is organized into three parts which focus on 1) psychoeducation about stigma as well as the intersection of substance use and criminal involvement, 2) contact with a peer recovery specialist, and 3) didactics around behavioral strategies (e.g., language, communication, validation) that can reduce stigma. The psychoeducation component was developed by drawing from multiple publicly available training curricula targeting substance use stigma (e.g., opioidlibrary.gov) as well as pertinent research that is used to challenge myths about addiction and criminal involvement. The contact component features a peer recovery specialist who shares personal experiences with substance use, incarceration, and stigma in Tennessee. Peer recovery specialists can have a wide range of roles, including facilitating connection to and delivery of behavioral health interventions as well as case management types of tasks; peer recovery specialists in Tennessee are certified through the Department of Mental Health and Substance Abuse Services. The behavioral strategies were drawn from literature on the use of stigmatizing language (Tran et al., 2018) as well as therapeutic strategies for interpersonal effectiveness, communication, and validation (Linehan, 1993). CSTARR-staff utilizes a mixture of visual aids (e.g., slides), media (e.g., video clips) and polls during the intervention. CSTARR-staff trainings are to be delivered for TN-ROCS staff in each county prior to the start of the CSTARR-client intervention in that county.

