#### Primary staff outcomes

We will examine change from the baseline to the three-month follow-up timepoint in the following measures:Perspectives on Stigma Reduction. The Perspectives on Stigma Reduction scale (PSR) is a 24-item internally developed measure that assesses perspectives on stigma (e.g., importance, impact on people involved in the criminal legal system) and stigma reduction strategies (e.g., openness to learning new strategies, use of nonjudgmental behaviors), among criminal legal professionals. 20 of the items are rated on Likert scales ranging from 1 (strongly disagree) to 9 (strongly agree), and 4 items are rated on a scale from 1 (0% of the time) to 9 (100% of the time). Items with the same response scales are summed to create total composite scores. Higher scores indicate more favorable views about stigma reduction.Difference and Disdain. The Difference and Disdain scale (DaD) (Corrigan et al., 2015b) is a 9-item measure that assesses how individuals view others in stigmatized groups compared to the general population. Responses are rated on a scale from 1 to 9, where 1 represents a belief that stigmatized people are similar to/favorable compared to others in the general population and 9 represents a belief that they are different from/unfavorable compared to the general population. We adapted this measure to ask about people with substance use problems and then criminal involvement (18 items total). Each scale ranges from 9–81 with higher scores indicating more differences/disdain. This measure has been shown to be valid for assessing public stigma in multiple studies (Corrigan, 2017; Corrigan et al., 2021).Social Distance. We use 10 items to assess desired social distance from people with a criminal background (separately asking about violent and nonviolent criminal histories) and 5 parallel items to assess desired social distance from people with histories of addiction. Items were adapted from the Bogardus social distance measure (Bogardus, 1933) to capture how staff would feel about interacting with (e.g., working, living next to, talking to, marrying) people with these backgrounds. Responses are rated on a Likert scale ranging from very uncomfortable to very comfortable, with the total score ranging from 10 to 50. Higher scores indicate less desired social distance. Variations of the Bogardus social distance items have been used widely and demonstrate good reliability and validity among various samples (Compton et al., 2006; Geisinger, 2010).Stigmatizing Attitudes Toward Criminal Involvement. The Attitudes Toward Prisoners scale (ATP) (Melvin et al., 1985) is a 36-item measure that assesses attitudes, beliefs, and negative stereotypes about “prisoners,” with responses rated on 5 point Likert scale from disagree strongly to agree strongly. We changed the word prisoners to “justice-involved people” throughout the scale to remove stigmatizing language but also because the staff we are targeting primarily work with people who are not currently incarcerated. Negatively worded statements are reverse coded for a summed total score ranging from 36 to 180. Higher scores indicate more positive attitudes toward people involved in the criminal legal system. The ATP has been used widely with criminal legal staff samples and demonstrates good internal consistency and validity (Kjelsberg et al., 2007; Ware et al., 2012).Beliefs About Addiction. The Addiction Beliefs Inventory (ABI) (Luke et al., 2002) is a 30-item measure containing 8 subscales that assess how people think about substance use, including beliefs about controllability, the disease model of addiction and genetic susceptibility, the need for professional treatment, how responsible someone with substance use is for their actions and recovery, self-medication, and beliefs about addiction being a moral weakness. Responses are rated on a 5-point Likert scale ranging from strongly disagree to strongly agree, with higher scores representing more agreement with the beliefs represented in the subscale. The ABI is often analyzed as subscales rather than a total score and demonstrates acceptable reliability and validity in multiple studies (Jordan et al., 2002; Luke et al., 2002).Opinions about Medication for Opioid Use. An adapted version of the Opinions about Medication-Assisted Treatment scale (aOAMAT) (Friedmann et al., 2016) will be used to evaluate how staff think about the treatment of OUD with methadone and buprenorphine among legally-involved populations. Responses are rated on a 6-point Likert scale (1 = strongly disagree, 5 = strongly agree, and we added a sixth response option if they had never heard of the medications). Methadone and buprenorphine were included in the same item to reduce the measure’s length, and naltrexone was not included (e.g., “Methadone and/or buprenorphine should be available as a lifelong treatment option”). This collapsed the 18 original items into 9; 2 additional items were added regarding the administration of medications during incarceration. This adapted measure has been shown to be reliable and valid with criminal legal staff ([name] et al., 2022).

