
#### Secondary staff outcomes

We will examine change from the baseline to the 3-month follow-up timepoint in the Dual-Relationship Inventory-Short Form (DRI-SF) (Gochyyev & Skeem, 2019), a 9-item measure adapted from the DRI and DRI-revised (Skeem et al., 2007) that was originally designed to be used in parallel forms with probation officers and their clients. The DRI assesses qualities of the relationship and working alliance between probation officers and clients. Responses are rated on a scale ranging from 1 (never) to 7 (always), with total scores ranging from 9 to 63. Higher scores indicate better relationships with clients. The DRI-Revised has been shown to be valid and internally consistent in a sample of probation officers and clients (Skeem et al., 2007). The DRI-SF has psychometrically sound properties comparable to the original DRI-R and has been validated in samples of probation officers and treatment staff (Gochyyev & Skeem, 2019).

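### For the staff client-relationship scale and the percentage-of-time items, the four-wave time test includes a post-test issued before the training ends, and a shift there is not interpretable as changed behaviour

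*Protocol article*

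**What the plan says.** **Timing.** Under Content and structure, "CSTARR involves a 4-h synchronous virtual training delivered via Zoom videoconferencing software". Under CSTARR-staff, the anonymous feedback survey fills the last 10 minutes of that session, and staff "are sent a link to complete the post-test survey at that time". The section gives no window for completing the survey, and it adds: "Email and phone call reminders will be used to increase completion of online surveys".

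**Measures.** Under Primary staff outcomes, the 24-item PSR covers views on stigma and on stigma reduction strategies, including the use of nonjudgmental behaviours. Of its items, "4 items are rated on a scale from 1 (0% of the time) to 9 (100% of the time"; items that share a response scale are summed, so these four form their own composite. Under Secondary staff outcomes, the DRI-SF has 9 items scored from 1 (never) to 7 (always), and "The DRI assesses qualities of the relationship and working alliance between probation officers and clients". Both sections name change from baseline to 3 months as the outcome.

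**Analysis.** Under Effectiveness, staff and client assessments go into "repeated measures factorial ANOVAs that compare pre, post-, 1-month, and 3-month follow-up data for clients and staff". Tukey comparisons then locate differences between timepoints. An effect counts as significant at p < 0.10 together with a meaningful effect size. Study design overview lists the same four timepoints for staff-level outcomes.

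**Rationale.** Under Social/public stigma, the authors argue that "attitude change is not only challenging, but potentially not as meaningful as behavior change".

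**The concern.** An attitude can change during a training session, so an immediate post-test is informative for the attitude scales. How often someone behaves in a certain way with clients, or how good the relationship with clients is, can change only through contact with clients. A staff member who answers the post-test when the link arrives has had none since baseline that the training could have altered. If the rating moves, the likely reasons are that the training changed how the person judges past conduct, that the answer expresses intention, or that it is meant to please the trainers. The shift can go either way, since training may lead staff to judge their earlier conduct more harshly.

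The four-wave analysis treats this wave like any other. A movement confined to it can make the time effect significant and can be picked out by the post hoc step. The article presents behaviour as what earlier stigma interventions neglected, and the results are meant to inform a larger randomised trial. An apparent early gain in staff behaviour would therefore carry weight that it has not earned.

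**Working it through.** The article gives no power or error-rate figure on this point, so there is none to reproduce. The check has two parts.

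**1. Which contrasts are affected**

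- Timepoints: 4 (pre, post, 1 month, 3 months), from Effectiveness.
- Pairs: 4 × 3 / 2 = 6. Those that involve the post-test: 3.
- Without the post-test: 3 × 2 / 2 = 3 pairs, none affected.
- The named outcome contrast, baseline to 3 months, is among the unaffected pairs.

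**2. How easily a shift at the post-test alone yields significance**

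Inputs from the article: 72 staff (6 counties × 12); 75% retained at 3 months, so n = 0.75 × 72 = 54; threshold 0.10.

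Assumptions, not in the article: standardised SD of 1, equal correlation ρ between waves, and true means of (0, d, 0, 0), so that only the post-test moves.

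*Overall time test.* Noncentral F with df1 = 3, df2 = 3(n − 1) = 159 and λ = n × Σ(μ_j − mean)² / (1 − ρ). For means (0, d, 0, 0) the sum of squares is 0.75d². At ρ = 0.5 this gives λ = 54 × 0.75d² / 0.5 = 81d².

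| d | λ (ρ = 0.5) | P(reject), ρ = 0.5 | λ (ρ = 0.7) | P(reject), ρ = 0.7 |
|---|---|---|---|---|
| 0.2 | 3.24 | 0.41 | 5.40 | 0.59 |
| 0.3 | 7.29 | 0.72 | 12.15 | 0.90 |
| 0.5 | 20.25 | 0.99 | 33.75 | > 0.99 |

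With the post-test left out, the three remaining means are equal and the test rejects at its nominal 0.10.

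*Pre-post Tukey pair.* The critical value for four means at 0.10 is 3.267 / √2 = 2.31. The noncentrality is dz × √54, where dz is the shift divided by the SD of the change. At ρ = 0.5 the SD of the change is √(2 × 0.5) = 1, so dz equals d and the two calculations are on the same scale. Probabilities use a noncentral t with 53 df.

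| dz | dz × √54 | P(pair declared different) |
|---|---|---|
| 0.2 | 1.47 | 0.21 |
| 0.3 | 2.20 | 0.46 |
| 0.5 | 3.67 | 0.91 |

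A normal approximation gives nearly the same values; at dz = 0.5, P(Z > 2.31 − 3.67) = 0.91.

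These probabilities concern the p-value only. The article also asks for a meaningful effect size but sets no threshold for it.

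**The case against.** **The declared outcome is already right.** Both outcome sections name baseline to 3 months, and the change score under Effectiveness also uses the 3-month survey. A reader might infer that the primary PSR outcome or the secondary DRI-SF outcome is invalid. The documents do not support that: at 3 months behaviour can have changed. The objection stands and confines the point to the overall time test and the pairs that involve the post-test.

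**An early shift could still be real.** The article fixes when the link is sent, not when the survey is completed, and it provides for reminders. Late responders may have seen clients. It would therefore go too far to say that a pre-post shift cannot be behaviour change. The statement holds for surveys answered when issued. A mixture of early and late responders does not make the wave easier to read.

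**The item content is inferred.** No PSR item is shown, nor its recall period. That the four items ask about the respondent's own conduct follows from their anchors and the description of the scale. If they ask about intention, an immediate rating is legitimate. The DRI-SF part does not depend on this inference.

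**Loss of power.** A reader might infer that the extra wave weakens the test for a real later effect. In the same model (n = 54, ρ = 0.5), with a true effect of 0.3 at 1 and 3 months and the post-test at baseline, power is 0.83 with four waves and 0.72 with three, so it rises. With the post-test half shifted it is 0.68, a small loss. Power is no general reason to remove the wave; the reason is what a significant result would be taken to mean.

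**Interpretation is already limited.** Potential limitations admits the lack of a control group and the reliance on self-report, effectiveness is a secondary goal of this pilot, and the authors nowhere say that they will read the immediate post-test as behaviour change. This lowers the stakes. But that section does not mention timing, and the analysis as written does not separate these measures from the attitude scales.

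**Conclusion.** The concern holds in a limited form. For the DRI-SF, and for the four-item PSR composite as far as its description shows, the overall four-wave time test and 3 of the 6 post hoc pairs are not interpretable as change in behaviour or relationships. The baseline-to-3-month contrast is unaffected, and so are the attitude scales.

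Under a shift at the post-test alone, the overall test rejects with probability 0.41 to 0.99 (d from 0.2 to 0.5, ρ = 0.5, n = 54), against 0.10 without that wave. The pre-post pair rejects with probability 0.21 to 0.91 over the same range. The sizes of shift and the correlation are assumptions, so these figures show how the problem scales and do not predict what the trial will find. The conclusion about interpretation rests on the timing and the constructs, not on these figures.

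**What to change.** Add to the Effectiveness section that, for the DRI-SF and the PSR percentage-of-time composite, the time test and post hoc comparisons use baseline, 1 month and 3 months, with baseline to 3 months as the named contrast, and that the immediate post-test of these two measures is reported descriptively only. Keep all four waves for the attitude measures.

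This brings the analysis into line with the outcome definitions. It needs no new data and no change to the surveys. The cost is that these two measures have no short-term inferential estimate, which would be of little value for them.
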